For several years, the French Société de Néphrologie Pédiatrique (SNP) has been coordinating a working group whose aim is to foster active research on INS. In addition to the prospective ongoing or achieved clinical trials coordinated by SNP members (NEPHROMYCY NCT01092962, NEPHRUTIX NCT01268033, RITUXIVIG NCT03560011, NEPHROVIR3 NCT02818738, OBIRINS NCT05786768), the group’s objective is now to develop a national coordinated long-term clinical research program for children treated for INS in SNP-affiliated centers until 18 years old [8]. This research program is based on a Trials within Cohorts (TwiCs) model and relies on a national retrospective-prospective cohort known as the PIN’SNP cohort that will enable and facilitate the implementation of multiple clinical trials within it.

Relton et al. developed the concept of TwiCs to tackle some of the difficulties associated with “classic” randomized controlled trials (RCTs): poor and slow accrual of patients, dropout rates, and limited external validity [9].

The TwiCs design uses a prospective cohort in which multiple pragmatic randomized trials may be embedded. For each trial, eligible patients are identified within the cohort and randomized between an interventional and control group. Patients of the interventional group are offered the experimental intervention, while patients of the control group still receive routine care. Data from the control group are available without any additional work since outcome measures are collected within the cohort’s usual follow-up and compared between the experimental and control groups.

In a rare chronic disease context, this design could be more efficient for conducting multiple clinical trials than implementing successive “classical” randomized controlled trials. It could, therefore, provide answers more rapidly to scientific questions specific to INS in children.

This paper aims to describe the PIN’SNP cohort and research program as well as the TwiCs design adapted to French regulatory requirements.

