### Consent management

During standard-of-care hospitalization or consultation at disease onset or during a follow-up visit, investigators describe the objectives of the cohort and platform to the relevant patients and, after a period of reflection, obtain the written consent of parents and the assent of minor patients to participate in the research. To facilitate future trials nested within the PIN’SNP cohort, patients and parents are solicited (i) to be included in the cohort and (ii) to be recontacted to receive specific information on future trials for which their child could be eligible.

If patients and parents agree to be recontacted, they are informed that they will be solicited to participate in an interventional trial either in the control group or in an experimental one in the future. For each future trial, specific information and consent will be implemented.

If patients and parents do not accept to be recontacted, they are only included in the cohort and will not be solicited to participate in any nested trial.

The original TwiCs design, where patients enrolled in the control group receive no specific information, has been adapted, as required by the French Ethics Committee, to provide information, when time comes, on each nested trial to all eligible patients before randomization in the experimental and control groups.

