	Adult outcome	Assess the impact of childhood onset NS in adulthood	Yes

Despite all its advantages, the PIN’SNP platform design will not systematically replace all future classical randomized controlled trials. The future implemented trials in the cohort will be pragmatic trials centered on effectiveness and rely on data collected from routine care for the control group. They will, therefore, be studies complementary to “conventional” randomized controlled trials, where experimental conditions can be fully controlled. The PIN’SNP platform is not built to run explanatory trials centered on efficacy with double-blinding and placebo. In addition, given the network on which this cohort is built (mostly third level centers of French pediatric nephrology units), relapsing patients will be over-represented among all INS patients included, as patients with no relapse are rarely referred to a reference center, if they live far from it. Therefore, the PIN’SNP platform is not designed to run a population-based cohort study.

However, this complementary approach will be based on a robust methodology, and the results will be reported in compliance with the CONSORT routine, developed explicitly for reporting randomized controlled trials using cohorts and routinely collected data [14].

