In the UK, the National Unified Renal Translational Research Enterprise: Idiopathic Nephrotic Syndrome study (NURTuRE-INS [21]) is a prospective cohort study of children and adults with biosamples and detailed clinical data for 739 INS patients from across the UK. The NURTuRE-INS cohort aims to pioneer innovative approaches for stratifying INS patients, deepening insights into the disease, and advancing research into its underlying mechanisms. The work conducted within this cohort complements that of our team and will undoubtedly contribute to the design of future nested trials within the PIN’SNP cohort.

While the PIN’SNP cohort is designed with a nationwide scope, it will inevitably face challenges in addressing rare or extremely rare conditions (e.g., INS in very young infants or anti-CD20-resistant NS). An international network could be envisioned, built upon the collaboration of several—or potentially all—of the previously mentioned cohorts. But before including a first patient in a prospective study within such a consortium of cohorts, many issues will have to be addressed such as international funding, patient consent management based on national regulations (included international use of e-consent), and coordination of reglementary approvals across different countries. Given the challenges associated with such tasks, we plan to start at the national level before considering moving to a European and/or international level.

The PIN’SNP platform features several methodological modifications compared with a conventional TwiCs design. In classical TwiCs studies, information is provided only to the patients randomized in the experimental arm. As a result, only patients in the experimental group can refuse the intervention. This refusal can lead to non-compliance within the experimental arm, constituting a methodological challenge that requires careful sample size planning. Additionally, it can introduce bias in estimating the average causal effect of the received treatment [16]. In the PIN’SNP platform, as information will be given to both control and interventional arms, non-compliance will likely be randomly distributed over study arms. It will not be necessary to manage the anticipated non-compliance rate in the intervention group and how it affects the choice and definition of the analysis methods and the sample size calculation or adaptation [16].

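### Informing both arms before randomisation reduces refusal, but it does not justify exempting nested trials from handling non-compliance in analysis and sample size

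*Protocol article*

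**What the plan says.** The Discussion paragraph on modifications to the conventional TwiCs design starts from the classical problem: only experimental-arm patients are informed, so only they can refuse. That refusal calls for careful sample size planning and can bias the estimated effect of the treatment received. The article then says that on this platform, where both arms are informed, "non-compliance will likely be randomly distributed over study arms". From this it concludes: "It will not be necessary to manage the anticipated non-compliance rate in the intervention group". The exemption also covers "how it affects the choice and definition of the analysis methods and the sample size calculation or adaptation".

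Four other statements bear on it:

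- Consent management: the adaptation is "to provide information, when time comes, on each nested trial to all eligible patients before randomization in the experimental and control groups". The same section adds: "For each future trial, specific information and consent will be implemented". It does not say explicitly that this consent is signed before randomisation.
- Introduction, describing TwiCs in general: "Patients of the interventional group are offered the experimental intervention, while patients of the control group still receive routine care".
- Discussion: the platform is "not built to run explanatory trials centered on efficacy with double-blinding and placebo".
- Statistical aspects: each nested trial will have its own analysis plan. No nested-trial sample size, power, effect size or non-compliance rate is given.

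**The concern.** The argument has two steps, and neither carries the conclusion.

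The first step is from informing both arms to non-compliance that is alike in both arms. Early information acts on refusal. It does not act on what happens after allocation. In an open comparison with routine care, experimental patients may not start the intervention or may stop it. Controls have no trial treatment to decline; they can depart from allocation only by obtaining the experimental option, with their care set by the referring physician (Procedures). These are different processes, and nothing in the document makes their rates equal.

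The second step is from alike in both arms to no need for an allowance. This fails even if the first step is granted, because departures in the two arms add up in the intention-to-treat contrast. Nor do equal rates make those who comply in one arm comparable with those who comply in the other, so the bias that the article names for classical TwiCs is not removed by balance alone.

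What is at stake is the planning of nested trials still to come. Authors who follow the statement and size a trial on the effect under full compliance would report more power than they have.

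**Working it through.** The document gives no nested-trial figure to reproduce, so the check is algebra followed by an illustration on stated assumptions.

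**Assumptions (not from the document).** Two-sided alpha 5%, 1:1 allocation, sample size set for 80% power at full compliance, and non-compliers have the outcome of the other arm. The rates p and q are assumed.

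**Dilution.** Let the full-compliance risks be πC (control) and πE (experimental), with Δ = πC − πE.

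- Observed experimental-arm risk: (1 − p)πE + pπC = πE + pΔ
- Observed control-arm risk: (1 − q)πC + qπE = πC − qΔ
- Intention-to-treat difference: Δ(1 − p − q)

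Setting p = q gives Δ(1 − 2p), not Δ.

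**Power and sample size.** With variance held constant, power = Φ[(1.960 + 0.842)(1 − p − q) − 1.960], and the required sample size is multiplied by 1/(1 − p − q)². For p = 10%, q = 0: 2.802 × 0.90 − 1.960 = 0.562, and Φ(0.562) = 0.713; 1/0.90² = 1.23.

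| p | q | 1 − p − q | Power | Sample size multiplied by |
|---|---|---|---|---|
| 0 | 0 | 1.00 | 80.0% | 1.00 |
| 5% | 0 | 0.95 | 75.9% | 1.11 |
| 10% | 0 | 0.90 | 71.3% | 1.23 |
| 20% | 0 | 0.80 | 61.1% | 1.56 |
| 30% | 0 | 0.70 | 50.0% | 2.04 |
| 5% | 5% | 0.90 | 71.3% | 1.23 |
| 10% | 10% | 0.80 | 61.1% | 1.56 |
| 20% | 20% | 0.60 | 39.0% | 2.78 |

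**Cross-check on a binary outcome.** Assume relapse of 60% against 40%. Full compliance needs 97 per arm for 80% power. With p = 10%, 20% and 30% and q = 0, the experimental-arm risk becomes 42%, 44% and 46%. Power at 97 per arm falls to 71.1%, 60.8% and 49.7%, and 120, 152 and 199 per arm would be needed. With 10% in each arm the risks are 58% and 42%, power is 60.7%, and 153 per arm would be needed. Assumed risks of 70% against 50% and of 50% against 30% give similar losses.

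Under these assumptions, a given rate of crossover in both arms costs more power than the same rate of non-uptake in the experimental arm alone (61% against 71% at 10%).

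**The case against.** The strongest defence is that the article is discussing refusal of the TwiCs kind, and on that it is largely right. Families are informed before allocation and asked for trial-specific consent. If they sign before randomisation, those who would refuse are never randomised and the classical problem mostly disappears. This stands, with two limits: the timing of consent is not explicit, and the exemption is worded for non-compliance in general.

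Second, the text is Discussion prose, and each nested trial will have its own analysis plan submitted to the authority and the Ethics Committee. That is true and limits the harm. But the exemption is a stated property of the design, not a detail left for later, and future plans may rely on it.

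Third, the figures for crossover in both arms require that controls can obtain the experimental treatment and its full effect. Where they cannot, q is 0 and only the one-sided rows apply. That also stands, though p then remains with nothing to offset it.

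A reader might go further and infer that nested trials will be underpowered. The document does not support that. It gives no sample size, effect or rate, and it describes the future trials as pragmatic and centred on effectiveness; a trial sized on an effect that already includes routine non-adherence would lose no power. A reader might also infer that biased per-protocol or as-treated analyses are planned. None is proposed. Nor does the article assert random distribution as a certainty: that sentence is hedged as likely. Only the conclusion drawn from it is unhedged.

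**Conclusion.** The exemption is wrong as written. Information before randomisation is a real gain, but it reduces refusal rather than removing non-compliance, and similar rates in both arms would not make an allowance unnecessary.

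The consequence is conditional. A nested trial risks being underpowered if it is sized on the full-compliance effect and p or q is above zero. On the assumptions above, 80% design power becomes about 71%, 61% or 50% for experimental-arm non-uptake of 10%, 20% or 30%, and about 61% for 10% in each arm. The direction follows from the algebra; the size depends on rates that the document does not give. No existing calculation is invalidated, because the first nested trial had not been launched when the article was written.

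**What to change.** Replace the two Discussion sentences, the one on random distribution and the one on not needing to manage non-compliance, with text that says:

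1. Information and consent before randomisation reduce refusal after allocation but do not remove non-uptake, discontinuation or crossover.
2. Trial-specific consent is obtained before randomisation. Consent management should say the same.
3. Each nested trial analyses by intention to treat. It gives its power or detectable effect at the effect expected after assumed non-uptake and crossover, with the assumed rates for each arm, or it says that the assumed effect already includes them.

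A complier-average estimate may be added as a supplementary analysis; it is optional.

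The cost is wording, plus a stated power or detectable effect that looks less favourable. In the binary example, keeping 80% power at 20% non-uptake means 152 instead of 97 per arm, or 2 × 55 = 110 more patients. That is noticeable beside the roughly 120 inclusions a year planned for the whole cohort, so a trial may prefer to keep its size and report the larger detectable effect.
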